#### Other Variables

Participant satisfaction with the intervention will be measured with an adapted Dutch version of the Client Satisfaction Questionnaire-short form (CSQ-8) [62,63]. The internal consistency of this scale in the Dutch population is very high (Cronbach alpha =.93). The 8-item self-report questionnaire has a scale ranging from 1 to 4 and a total score range from 8 to 32.

Furthermore, participants will be asked about important life events and whether they are currently receiving treatment from a mental health specialist.

### Sample Size

Depressive symptoms and well-being are used as a starting point for the power calculation. We aim to be able to show differences between Psyfit and the waiting list control condition with a standardized effect size (Cohen’s *d*) of 0.33 or larger. A standardized effect of 0.33 can be considered as the lower limit of a moderate clinical effect [64] and is based on a meta-analysis of well-being intervention research [35] and a recent randomized controlled trial [36]. To demonstrate this effect, and assuming an alpha of 0.05 and a statistical power (1-Beta) of 80%, we need 145 participants in each condition; therefore, we need 290 participants in total for the trial.

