**Methods:**

In this two-armed randomized controlled trial, a total of 290 participants will be assigned to use Psyfit (experimental condition) or to a 6-month waiting list (control condition). Adults with mild to moderate depressive symptoms interested in improving their mental fitness will be recruited from the general population through advertisements on the Internet and in newspapers. Online measurements by self-assessment will be made prior to randomization (pre-test), 2 months after baseline (post-test), and 6 months after baseline (follow-up).

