### Randomization

The online randomization procedure will be carried out at the individual level. After returning the informed consent form and completing the baseline questionnaire, people who meet the inclusion criteria will be randomly allocated to the experimental group (Psyfit) or to the waiting list and they will be notified by email. Randomization will be stratified by gender, education, and severity of symptoms based on CES-D scores (scores between 10-15 and 16-24). A computer program will allocate participants using a generated randomization list. Block randomization in blocks of two will be performed to ensure equal distribution of participants across conditions.

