### Assessments

The primary outcome measure is well-being. Secondary outcome measures include depressive symptoms, general health and vitality, and economic costs (as measured by health care use, days of absence, inefficient job performance, and work productivity). For an overview of outcomes and instruments, see Table 1.

Measurements will be taken at baseline (pre-test), directly after the intervention (post-test, 2 months after baseline), and 6 months later (follow-up). All measurements are self-report measures and will be administered via email with a link to the questionnaire on the Internet.

High dropout rates are a characteristic feature of online trials and can be as high as 50% [50]. Therefore, email reminders and rewards (eg, raffle of six iPods and vouchers) for filling in the questionnaires will be used. It is expected that this will lead to a lower attrition rate.

**Table 1 table1:** Questionnaires and assessment times.

		T0	T1	T2
Questionnaire^a^	Measurement	Pre-test	Post-test^b^	Follow-up^c^
MHC-SF	Well-being/positive mental health	X	X	X
WHO-5	Well-being	X	X	X
CES-D	Symptoms of depression	X	X	X
MOS SF-36 subscales	Vitality and general health	X	X	X
TIC-P and PRODISQ	Health service uptake and production losses	X	X	X
CSQ-8	Client satisfaction		X	
Demographics	Age, gender, education, marital status, job status	X		

^a ^all questionnaires are discussed within Instruments section

^b ^2 months after T0

^c ^6 months after T0

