The economic evaluation will be conducted from a societal perspective, thus including the intervention costs (ie, Psyfit), the costs of health care uptake (TIC-P), the participants’ out-of-pocket costs for obtaining health care (TIC-P), and the economic costs due to productivity losses in paid work (PRODISQ). The incremental cost-effectiveness ratio (ICER) will be calculated. Uncertainty in the ICER will be captured using a bootstrap approach, producing a scatter of simulated ICERs over the ICER-plane and by drawing an ICER acceptability curve of the likelihood that Psyfit is more cost-effective for a range of willingness-to-pay (WTP) ceilings.

All analyses will be conducted using two-sided tests and alphas of .05. For this purpose, the most recent version of the SPSS software will be used.

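### The 290 to be randomised is the complete-data sample size: the stated 80% power has no allowance for the dropout the protocol expects

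*Protocol article*

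**What the plan says.** The Sample Size section takes a standardised effect of 0.33, of which it says "A standardized effect of 0.33 can be considered as the lower limit of a moderate clinical effect". It derives the number needed "assuming an alpha of 0.05 and a statistical power (1-Beta) of 80" per cent and concludes: "we need 145 participants in each condition; therefore, we need 290 participants in total for the trial". Dropout is not mentioned there.

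The other parts of the article that bear on this are:

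- **Abstract, Methods:** "a total of 290 participants will be assigned to use Psyfit (experimental condition) or to a 6-month waiting list". So 290 is the number randomised, not the number expected to finish.
- **Randomization:** "Block randomization in blocks of two will be performed to ensure equal distribution of participants across conditions", which means 1:1 allocation.
- **Assessments:** "High dropout rates are a characteristic feature of online trials and can be as high as 50" per cent. Reminders and rewards are expected to bring attrition down, but no rate for this trial is given.
- **Analysis:** the main comparison is a regression of each outcome on a treatment dummy, and no baseline covariate is named for it. Dropout is anticipated, and missing post-test and follow-up scores are to be filled in by EM, with completers-only and per-protocol analyses as sensitivity analyses. Also: "All analyses will be conducted using two-sided tests and alphas of .05".
- **Discussion:** dropout is the first limitation listed.

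**The concern.** A sample size that is to deliver 80% power after dropout must be larger than the complete-data requirement, or must rest on some stated gain in precision that pays for the loss. Here the complete-data requirement and the number randomised are the same figure, and no gain is claimed. Yet the same article tells the reader to expect loss, possibly heavy loss.

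What is at stake is how the result is read. The effect of 0.33 is described as the bottom of the clinically moderate range, so the shortfall falls on the very effect the trial is meant to detect. If the trial is not significant, a reader who trusts the Sample Size section will weigh that result as if an effect of 0.33 had an 80% chance of being found. With incomplete data the chance may be clearly lower.

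**Working it through.** **Inputs from the article.** d = 0.33, alpha 0.05, power 80%, 145 per arm (Sample Size); two-sided tests (Analysis); 1:1 allocation (Randomization); 290 assigned (Abstract); 50% as the upper figure for online trials in general (Assessments).

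**Assumptions of this review.** Equal loss in both arms, unrelated to outcome; loss rates of 10 to 40%, which the article does not give; a baseline–outcome correlation r = 0.5, which it does not give either.

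**Step 1: reproduce the plan's figure.** n per arm = 2(z₀.₉₇₅ + z₀.₈₀)² / d² = 2(1.960 + 0.842)² / 0.33² = 144.2, rounded up to 145. This matches with zero loss. Power at 145 per arm is 80.2% by the normal approximation and 79.97% by the noncentral t.

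**Step 2: is a margin hidden in the 145?** A one-sided test would need 114 per arm, and 145 would then absorb 1 − 114/145 = 21% loss. The Analysis section fixes two-sided tests, so this route is closed and the whole sample is used up by the complete-data requirement.

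**Step 3: power after loss.** With m = 145 × (1 − loss) per arm, rounded down, the noncentrality is 0.33 × √(m/2) on 2m − 2 degrees of freedom. The detectable effect is the d that gives 80% power at the same m. For baseline adjustment, d is replaced by 0.33/√(1 − r²) = 0.33/√0.75 = 0.381, with one degree of freedom fewer.

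| Assumed loss | m per arm | Noncentrality (unadjusted) | Unadjusted power | Detectable d, unadjusted | Adjusted power, r = 0.5 |
|---|---|---|---|---|---|
| 0% | 145 | 2.81 | 80% | 0.33 | 90% |
| 10% | 130 | 2.66 | 76% | 0.35 | 86% |
| 20% | 116 | 2.51 | 71% | 0.37 | 82% |
| 30% | 101 | 2.34 | 65% | 0.40 | 77% |
| 40% | 87 | 2.18 | 58% | 0.43 | 71% |
| 50% | 72 | 1.98 | 50% | 0.47 | 62% |

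The normal approximation without rounding m differs by at most about a point (for example 51% unadjusted and 63% adjusted at 50% loss, and 87% adjusted at 10%). Holding about 80% at 50% loss would take r of about 0.7 (79%).

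**Step 4: does imputation change this?** Filling a missing score with a prediction from observed data brings the row count back to 290 but adds no independent information on that outcome. I simulated one simple version: a single conditional-mean fill from the baseline score, r = 0.5, loss completely at random, then the unadjusted test on all 290 rows.

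- With treatment left out of the imputation model, power at d = 0.33 was about 68% at 20% loss and 42% at 50%.
- With treatment included, the rejection rate was about 83% at both loss rates, but the type I error rose to about 9% and 24%.

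The apparent recovery in the second case comes from standard errors that are too small.

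**The case against.** Several points on the other side are fair, and they limit what may be claimed.

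- **The formula is right.** This stands. It is a planning allowance that is missing, not a sum that is wrong.
- **50% is not a forecast.** This stands. The article gives it as how high online trials can go and expects to do better. A reader might infer that the trial has only even odds of finding its target effect. The article does not support that, because even odds belong to the outer bound alone.
- **Baseline adjustment could pay for moderate loss.** This stands in part. Baseline scores are collected before randomisation, and at r = 0.5 power is still about 82% with 20% loss. So one cannot say that 80% is reached only at zero attrition whatever the model. But the main comparison names only the treatment dummy, and the sample size claims no covariate gain.
- **The figures are not those of the planned primary analysis.** This stands. They are complete-case power, which corresponds to the completers-only sensitivity analysis. The power of the EM analysis depends on an imputation model that the article does not describe. The simulation shows that this does not rescue the 80%: power was lower than complete-case power, or the rejection rate was bought with false positives.
- **Dropout is disclosed.** It is, in Assessments, Analysis and Discussion. None of these is connected to the power statement.
- **Low power biases neither the estimate nor the error rate, and a null result is read from its interval.** True, and for this reason a corrected statement is enough.

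**Conclusion.** The point holds in a limited form. For the unadjusted comparison that the plan names, 290 randomised gives 80% power for d = 0.33 only with complete outcome data, and the article itself does not expect complete data. Any loss takes that comparison below 80%: about 76% at 10% loss, 71% at 20%, and 50% at the article's upper figure, with the detectable effect rising to 0.35, 0.37 and 0.47.

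These sizes rest on equal loss unrelated to outcome, on loss rates assumed here (except the 50% bound), and on complete-case analysis. With baseline adjustment at an assumed r = 0.5, the claim survives 20% loss (82%) but not 30% (77%). The article supports neither a single figure for the power of this trial nor the reading that its sample size calculation is miscalculated.

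**What to change.** Keep 290 and restate the power in the Sample Size section, for example:

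> With 290 randomised, the trial has 80% power for d = 0.33 if outcome data are complete. Under assumed equal losses of 10, 20, 30, 40 and 50% (the last being the upper figure for online trials), unadjusted complete-case power is about 76, 71, 65, 58 and 50%, and the effect detectable with 80% power is about 0.35, 0.37, 0.40, 0.43 and 0.47. If the analysis adjusts for the baseline score, with an assumed baseline–outcome correlation of 0.5, complete-case power is about 86, 82, 77, 71 and 62%.

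Label the loss rates and the correlation as assumptions, and do not read a non-significant result against 80% power.

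The cost is one paragraph and a less favourable power statement. No extra participants are needed. For comparison, keeping 145 evaluable per arm would mean randomising 145/0.8 = 181.25, so 182 per arm (364 in total), at 20% loss, and 145/0.5 = 290 per arm (580 in total) at 50%.

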### Analysis

Results will be reported according to the Consolidated Standards of Reporting Trials (CONSORT) statement regarding eHealth [65,66]. We will adhere to the intention-to-treat (ITT) principle, which means all participants who have been randomized will be included in the analyses. Missing data at T1 and T2 will be imputed using the expectation-maximization (EM) method, as implemented in Statistical Package for the Social Sciences (SPSS) Missing Value Analysis. The program imputes missing values by maximum likelihood estimation using the observed data in an iterative process [67]. In online trials dropout is to be expected, and sometimes a large amount of missing data has to be estimated. Although ITT analysis is the approach of choice according to the CONSORT statement, there may also be pitfalls, such as when the missing-at-random assumption is not plausible and the results of the analysis are subsequently biased [68]. Therefore, a completers-only analysis and a per-protocol analysis will be conducted in addition (sensitivity analysis). Reasons for dropout in the study will be checked at random by telephone follow-up (dropout analysis).

To examine differences between the two conditions, we will use multiple regression analyses with the clinical outcomes on continuous measures (MHC-SF, WHO-5, CES-D, and the vitality and general health scales from MOS SF-36) as dependent variables and an intervention-control group dummy as predictor variable. We will compute standardized effect sizes (Cohen’s *d*). Cohen’s *d *is computed by subtracting the mean post-test intervention score from the mean post-test control group score and dividing the difference by the pooled standard deviation [69].

Moderator analyses will be conducted to examine which groups benefit more (or less) from the intervention by regressing the outcomes on independent variables such as gender, education, mild/moderate depressive symptoms, the treatment dummy, and the interaction with the treatment dummy and the selected independent variables.

The economic evaluation will be conducted from a societal perspective, thus including the intervention costs (ie, Psyfit), the costs of health care uptake (TIC-P), the participants’ out-of-pocket costs for obtaining health care (TIC-P), and the economic costs due to productivity losses in paid work (PRODISQ). The incremental cost-effectiveness ratio (ICER) will be calculated. Uncertainty in the ICER will be captured using a bootstrap approach, producing a scatter of simulated ICERs over the ICER-plane and by drawing an ICER acceptability curve of the likelihood that Psyfit is more cost-effective for a range of willingness-to-pay (WTP) ceilings.

All analyses will be conducted using two-sided tests and alphas of .05. For this purpose, the most recent version of the SPSS software will be used.

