## Discussion

This online trial will examine whether an Internet-based self-help intervention for the enhancement of well-being is effective in terms of clinical outcomes and economic costs. A second objective is to examine whether certain groups benefit more or less from the intervention. The enhancement of well-being on a large scale may contribute to public mental health by resulting in better health, fewer mental disorders, and enhanced quality of life on a population level [11,70].

This study has several *a priori *limitations. First, dropout may occur in either of the two groups. To examine any selectiveness, we will conduct dropout analysis and a telephone survey for examining reasons for dropout. Moreover, we will conduct intention-to-treat analyses in which missing values are replaced by their most likely estimates. Second, we will only use self-report questionnaires, not formal diagnostic instruments, to establish diagnoses. Therefore, we will not know whether participants meet the criteria for a Diagnostic and Statistical Manual of Mental Disorders (DSM-IV) diagnosis so results about prevention of mental disorders will not be available. We opted for self-rating because the intervention should be easily accessible and highly applicable because of its public nature. We don’t want to scare people off by intensive diagnostic procedures. A third limitation of this study concerns the use of questionnaires that are not (yet) validated for online purposes. Psychometric properties of online assessments may differ from their paper-and-pencil counterparts [71]. On the other hand, the CES-D [45] and the MHC-SF [52], which are used in this study, have been proven to be reliable and valid instruments even if used on the Internet. Finally, the open recruitment strategy may attract certain groups, for example, more higher-educated people or more spiritually engaged and higher-motivated people. Therefore, care must be taken in generalizing the results.

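### A single EM fill followed by ordinary regression treats imputed scores as observed: standard errors are too small if arm is in the EM model, and the effect is diluted if it is not

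*Protocol article*

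**What the plan says.** The Analysis section of the protocol article fixes the handling of missing outcomes: "Missing data at T1 and T2 will be imputed using the expectation-maximization (EM) method", using a named SPSS module. Under the intention-to-treat principle, "all participants who have been randomized will be included in the analyses". The comparison of arms is a multiple regression of each continuous outcome with "an intervention-control group dummy as predictor variable", accompanied by Cohen's d, the post-test mean difference divided by the pooled SD.

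The Discussion shows what kind of fill is meant. It describes "intention-to-treat analyses in which missing values are replaced by their most likely estimates", which is one point estimate per missing value.

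For the clinical outcomes the protocol states no multiple imputation, direct-likelihood analysis or variance correction. A bootstrap appears only in the economic evaluation: "Uncertainty in the ICER will be captured using a bootstrap approach". Completers-only and per-protocol analyses are added as sensitivity analyses because missing-at-random may not hold.

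On the amount of dropout, the Assessments section says "High dropout rates are a characteristic feature of online trials and can be as high as 50" percent, and of the planned reminders and rewards, "It is expected that this will lead to a lower attrition rate". No planning figure is given.

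**The concern.** EM is a sound way to estimate means and covariances from incomplete data. The fault lies in the next step. A most-likely value sits exactly on the fitted regression and has no residual scatter, yet ordinary regression counts it as a full independent observation. The residual variance is then too small and the effective sample size too large. The pooled SD in the denominator of Cohen's d shrinks for the same reason.

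If arm is not among the EM variables, the problem takes another form. Missing scores in both arms are filled from one common regression, so the filled part of the sample shows no treatment effect and pulls the estimate towards zero.

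This is the primary intention-to-treat analysis. The p-value, confidence interval and effect size for the main claim all come from the filled dataset.

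**Working it through.** **Plan's own figure.** For a standardized difference of 0.33, two-sided alpha 0.05 and 80% power, n per arm = 2(1.960 + 0.842)²/0.33² = 144.2, rounded up to 145. Power at 145 per arm is 0.802. The stated 145 per arm (290 in total) is reproduced and is not in dispute.

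**Inputs.** From the protocol: 145 per arm, effect 0.33 with SD 1, alpha 0.05 two-sided. Assumed, because the protocol gives no values: dropout fraction m from 0.10 to 0.50, equal in both arms and unrelated to scores; baseline/T1/T2 correlation r of 0.3, 0.5 or 0.7; normal scores.

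**(a) Arm in the EM model.** When a missing score is predicted from baseline and arm:

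- Group dummy only: true variance of the difference = (2/n)[r² + (1−r²)/(1−m)]. The variance that regression reports = (2/n)[r² + (1−r²)(1−m)].
- Baseline-adjusted: reported SE / true SE = 1−m, for any r.
- With k = reported SE / true SE, type I error = 2[1 − Φ(1.96k)].
- SD of the completed scores = √[r² + (1−r²)(1−m)], so the reported d = 0.33 divided by that SD.

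Example with r = 0.5, m = 0.5, dummy only. True SE = √(2/145 × 1.75) = 0.155 and reported SE = √(2/145 × 0.625) = 0.093. So k = 0.60 and type I error is about 0.24. Reported d = 0.33/√0.625 = 0.42.

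| Dropout | Dummy only, r = 0.7 / 0.5 / 0.3 | Baseline-adjusted | Reported d for true 0.33 (r = 0.5) |
|---|---|---|---|
| 10% | 0.063 / 0.070 / 0.075 | 0.078 | 0.34 |
| 20% | 0.080 / 0.097 / 0.110 | 0.117 | 0.36 |
| 30% | 0.102 / 0.133 / 0.156 | 0.170 | 0.37 |
| 40% | 0.131 / 0.181 / 0.218 | 0.240 | 0.39 |
| 50% | 0.169 / 0.241 / 0.295 | 0.327 | 0.42 |

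The closed form was checked by simulation under the null: 1,500 runs per cell, an EM conditional-mean fill, then ordinary least squares. Across the three correlations and both regression models, simulated type I error was 0.08-0.12 at 20% dropout, 0.10-0.19 at 30% (the top value with EM run separately by arm), 0.13-0.25 at 40% and 0.19-0.33 at 50%. The lowest 50% cell simulated at 0.185 against 0.169 in closed form. For r = 0.5 and 50% dropout, baseline-adjusted, the mean reported SE was 0.072 against an empirical 0.141.

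**Control.** On the same data, a baseline-adjusted regression on observed T1 scores alone had type I error of 0.03-0.06 at every dropout rate. The excess therefore comes from the fill.

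**(b) Arm omitted from the EM model.** Simulated type I error was 0.04-0.06. The filled fraction carries no arm difference, so the expected difference is about 0.33(1−m): 0.33 × 0.7 = 0.23 at 30% and 0.33 × 0.5 = 0.165 at 50%. The simulated values were 0.231 and 0.163. At 50% the reported SE was 0.072, so an interval around the average estimate ends at 0.163 + 1.96 × 0.072 = 0.30, below the true 0.33. These differences are in units of the true SD. Dividing by the shrunken SD recovers only part of the loss: 0.231/√0.775 = 0.26 and 0.165/√0.625 = 0.21.

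**The case against.** **No planning dropout rate exists.** A reader might infer that type I error will be several times nominal at the dropout this trial expects. The document does not support that. Its 50% is an upper figure for online trials in general, and the protocol expects to stay below it. Its remark about large amounts of missing data is also general and says only that this sometimes happens. The 50% row is a worst case, and at 10% dropout the inflation is modest. This objection stands, so the size has to be given as a range under assumptions.

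**Inflation is only one of two branches.** The protocol does not say whether arm is in the EM model. If it is not, the test keeps its level and the error runs against the intervention. This also stands. Inflated and diluted effects are alternatives and cannot both occur in one analysis. Neither alternative is acceptable, however.

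**Sensitivity analyses are planned.** The completers-only analysis has near-nominal error under the missingness simulated here, and a gap between it and the main result would be visible. It is justified by doubt about missing-at-random, though, whereas the variance problem is present even when that assumption holds. A secondary analysis does not correct the primary p-value.

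**The article is condensed.** Detail may be left to an analysis plan. Here the article positively names the method and describes the fill, so the point does not rest on an omission.

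**Cost-effectiveness.** A reader might also infer that the ICER scatter and acceptability curve inherit false precision. The protocol does not say that costs are filled before the bootstrap, and nothing was computed for costs. That part is conditional only.

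**Conclusion.** The point holds as a fault in the stated primary analysis. With arm in the EM model, the main test is anticonservative: type I error is about 7-8% at 10% dropout (correlation 0.5), 8-12% at 20%, 10-19% at 30% and 19-33% at 50%, and Cohen's d is overstated. With arm omitted, type I error stays near 5%, but the effect is diluted to about 0.23 at 30% and 0.16-0.17 at 50%, with intervals too narrow around the wrong value. These sizes rest on assumed dropout, correlations of 0.3-0.7, normal scores and dropout unrelated to scores or arm. The direction of each error follows from the method itself.

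**What to change.** In the Analysis section, replace the single EM fill as the primary intention-to-treat method with one of the following:

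- a likelihood mixed model on all observed T1 and T2 scores, including arm by time and the baseline score; or
- multiple imputation with arm and baseline scores in the imputation model, combined by Rubin's rules.

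Compute Cohen's d with an SD taken from observed scores. Amend the Discussion sentence on replacing missing values to match. If costs are also imputed, do so within each bootstrap resample and state that order. The covariance structure, further covariates and number of imputations are matters of choice, provided that they are fixed in advance.

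The cost is a change of wording, a little more programming and somewhat wider intervals. Recruitment, assessments and the stated sample size calculation are not affected by this change.

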 Functionalities in PsyfitGeneral self-test to assess individual well-being level beforehand and after 2 months.A personal plan in which the participant can reflect on his or her goals, motives, and pitfalls.A “mood meter” for monitoring changes in the mood of the participant. The outcomes are presented in a graph.Automatic email service twice a week with reminders, tips, and advice.Online community for sharing experiences and peer-to-peer support.Contact form: participants can ask questions and receive feedback from a psychologist via email. If required, the participant is referred to professional care. Technical assistance is also provided.“My Psyfit”: the participant can download and print out a personal PDF blueprint of the intervention with all the modules, exercises, and progress measurements completed.Videos: each module starts with a video showing a Dutch expert explaining the relevance of this particular module.Module self-tests: each module starts and ends with a short self-test to see if the particular skill has improved.

The participant can work through the intervention independently (self-help) but can fill in a contact form with a question if necessary. Psyfit could be likened to a toolbox from which people can “pick and mix” whatever they like and need. The web statistics module will systematically track and trace the actions of each participant, such as the number of log-on times, the time spent on the website, and the modules chosen. This enables adherence to the intervention to be examined.

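### The completers-only and per-protocol analyses are planned as the answer to a failed missing-at-random assumption, but neither relaxes it

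*Protocol article*

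**What the plan says.** The Analysis section commits to including everyone randomised, with missing T1 and T2 values filled in by EM in SPSS. It notes that much data may have to be estimated in an online trial. It gives as an example of a pitfall the case "when the missing-at-random assumption is not plausible and the results of the analysis are subsequently biased". The next sentence is the response: "Therefore, a completers-only analysis and a per-protocol analysis will be conducted in addition (sensitivity analysis"). The main comparison is a regression in which the only predictor named is the treatment dummy.

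Other parts of the protocol bear on this:

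- **Assessments** puts dropout in online trials at up to 50% and plans reminders and rewards to reduce it.
- **Analysis** and **Discussion** plan a telephone check of reasons for dropout; the Discussion adds a dropout analysis to look for selectiveness and accepts that dropout may occur in either group.
- **Intervention Group: Psyfit** says of the logged website use: "This enables adherence to the intervention to be examined". Only the experimental group can reach the site during the study.

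No analysis that departs from MAR is stated.

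**The concern.** A sensitivity analysis for missing data should vary the assumption that is in doubt. Here the doubtful assumption is MAR, and the word that opens the response presents the two added analyses as the answer to it. If both need assumptions at least as strong as MAR, they cannot show how the conclusion would change if MAR failed. Three analyses could then point the same way for the same wrong reason.

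This matters more than usual because the protocol itself expects substantial dropout, and because staying in an online self-help trial may well depend on how the participant is doing. The choice is stated in the text, so it is not a detail left to a fuller plan.

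**Working it through.** **1. The plan's own figure.** Inputs from Sample Size and Analysis: d = 0.33 ("A standardized effect of 0.33 can be considered as the lower limit of a moderate clinical effect"), "a statistical power (1-Beta) of 80"%, and "All analyses will be conducted using two-sided tests and alphas of .05". Then n per arm = 2 × (1.960 + 0.842)² / 0.33² = 144.2, rounded up to 145. This agrees with "we need 145 participants in each condition; therefore, we need 290 participants in total for the trial". The sample size is not in dispute; it supplies the scale for what follows.

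**2. What each analysis assumes.**

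| Analysis | Assumption needed for an unbiased group difference |
|---|---|
| EM imputation | Dropout unrelated to the missing outcome, given the observed variables in the imputation (MAR) |
| Completers-only, group dummy alone | Dropout unrelated to outcome within each arm: stronger than MAR |
| Completers-only with baseline covariates | MAR given those covariates: not weaker |
| Per-protocol | An assumption about missing outcomes as above, plus adherence unrelated to prognosis |

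Waiting-list participants have no access for 6 months, so selection on programme use can operate only in the Psyfit arm.

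**3. Can the three mislead together?** I simulated 2,000 trials per scenario with 145 per arm. Assumptions, none from the protocol: baseline–outcome correlation 0.6; dropout about 50% in Psyfit and 30% in control; adherence mildly related to outcome; per-protocol applied as observed controls against observed adherent Psyfit users. Mean estimated d:

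| Dropout mechanism | True d | EM | Completers | Per-protocol | All three significant |
|---|---|---|---|---|---|
| Low outcome drives Psyfit dropout only | 0 | 0.27 | 0.41 | 0.48 | 67% |
| Same | 0.33 | 0.60 | 0.74 | 0.80 | 99.6% |
| Low outcome drives dropout in both arms | 0 | 0.10 | 0.15 | 0.22 | 16% |
| Baseline drives Psyfit dropout (MAR) | 0 | 0.00 | 0.25 | 0.33 | 9% |
| Completely at random | 0 | 0.00 | 0.00 | 0.09 | 2% |

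With no missing data, a true null was rejected in about 5% of trials. Baseline-adjusted completers gave practically the same mean as EM in every scenario. The shares in the last column are indicative only: EM values treated as observed rejected in about 16% of null trials even when data were missing completely at random, which is a separate matter.

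Two things follow. All three analyses can be biased in one direction and significant together. And when MAR holds given baseline, EM is right while both checks are wrong.

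**4. What a departure from MAR would do.** Let f be the share missing in Psyfit and delta the amount, in SD, by which those participants do worse than MAR predicts, with no departure in controls:

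effect = 0.33 − f × delta; zero at delta = 0.33 / f

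| f (assumed; 50% is the protocol's upper figure) | delta 0.20 | delta 0.33 | delta 0.50 | delta at zero effect |
|---|---|---|---|---|
| 50% | 0.23 | 0.165 | 0.08 | 0.66 |
| 30% | 0.27 | 0.23 | 0.18 | 1.10 |
| 20% | 0.29 | 0.26 | 0.23 | 1.65 |

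Significance goes sooner. Even as if all 290 were observed, the unadjusted standard error is √(2/145) = 0.117, so d must exceed 1.96 × 0.117 = 0.23. That margin of 0.10 is used up at delta = 0.10/f: 0.20, 0.33 and 0.50 SD for the three rows.

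A departure in controls offsets this: effect = 0.33 − f_P × delta_P + f_C × delta_C. With f_P = 50%, f_C = 30% and a common delta of 0.33, it is 0.33 − 0.165 + 0.099 = 0.264. Delta therefore has to be varied by arm.

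**The case against.** The protocol does more about dropout than these two analyses. It plans reminders and rewards, a telephone check of reasons, and a dropout analysis, and it lists dropout first among its limitations. MAR failure is offered as one example of a pitfall, and completers-only is a fair way to see whether the result hangs on imputed values. All of that stands. But the telephone check collects reasons rather than outcomes, the dropout analysis can compare only observed characteristics, and neither enters a stated effect estimate. They help to judge whether MAR is plausible; they do not show what follows if it is not.

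A reader might infer more than the document supports:

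- **That the three analyses must agree, or have no value.** In the simulation they spread (0.27, 0.41 and 0.48 in the first scenario). Disagreement can hint at outcome-related dropout, and completers-only can be unbiased in special cases, for example no effect and the same dropout mechanism in both arms.
- **That the bias must favour Psyfit.** This presumes selective loss in one arm. The Discussion expects that dropout may occur in either group, and with outcome-driven loss in both arms the EM bias falls from 0.27 to 0.10. Not responding to a questionnaire is also not the same as gaining nothing from the programme, since questionnaires are emailed separately.
- **That per-protocol sets motivated users against all controls.** The article does not define the per-protocol set. If a completed post-test is also required, controls are selected too.
- **That agreement will be reported as proof of robustness.** The document does not say so.

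**Conclusion.** The point holds in a limited form. The protocol names a threat and fixes a remedy that does not meet it: completers-only needs an assumption at least as strong as MAR, and per-protocol adds selection after randomisation. Agreement of these analyses with the intention-to-treat result would not be evidence of robustness to MAR failure.

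The conclusion about assumptions follows from the analyses named and does not depend on the simulation. The sizes do depend on assumptions. The zero-effect values of 0.66, 1.10 and 1.65 SD rest on an estimate equal to the planned 0.33, on the assumed shares missing, and on a departure in the Psyfit arm only. The protocol gives no expected dropout rate for this trial, so the range is all that can be stated. The matter should be corrected, but it does not undermine the design.

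**What to change.** Keep completers-only and per-protocol as supplementary analyses, and stop describing them as the check on MAR. For the primary well-being outcome, add a multiple imputation under MAR followed by delta adjustment. Shift the imputed values in steps, separately in each arm, and report the combinations at which the primary conclusion changes. Reference-based imputation for Psyfit dropouts, in which their missing outcomes follow the control distribution, is a useful optional companion. The telephone reasons and the dropout analysis can then inform which deltas are credible.

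A complier-average effect from the usage log may look like a natural replacement for per-protocol, but it does not serve this purpose. It still needs an assumption about missing outcomes. It also requires that assignment does nothing for non-adherers, which is doubtful when they receive regular emails and have the self-tests and the online community available.

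The cost is some added programming and no new data collection. The downside is that the resulting statement on robustness may be less favourable.
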